**Fig 1 pone.0332387.g001:**
[figure not shown]
Study schedule of EPSILON IE. Essentially, the screening period is set at 30 days and the investigational testing period after insertion is a maximum of 2 weeks to facilitate testing and provide sufficient time for non-provoked spontaneous seizures to occur. The post-observation period (1 week) is judged as sufficient for monitoring potential adverse events associated with endovascular and intracranial implantation of electrodes. *Not required if epileptic seizures occur within one week of placement of the test device. ** EP-01 will be left in place until the onset of epileptic seizures or for a maximum of 14 days (plus 3 days). ***If the trial is to be stopped during the clinical trial inspection period, the tests specified at the time of removal of the EP-01 will be carried out as much as possible depending on the subject’s condition, the EP-01 will be removed, and the trial will move to the post-observation period. Suppose the trial is to be stopped during the post-observation period. In that case, the tests specified one week after removal of the test device will be carried out as much as possible depending on the subject’s condition, and the trial will then end. **** Only subjects who underwent epilepsy resection were included. ***** If the measurement is conducted within 90 days before obtaining consent, there is no need to remeasure, and data from before consent was obtained will be collected. ****** When only EP-01 or both EP-01 and intracranial electrodes are indwelled, EEG data from EP-01 and intracranial electrodes will be recorded under video surveillance. EEG data during eyes opening and closing (the investigator, etc. will decide the timing of EEG data acquisition during eyes opening and closing) and EEG data during epileptic seizures will be submitted to the Central Evaluation Committee.

This protocol has been described in accordance with the SPRIT checklist (Standard Protocol Items: Recommendations for Interventional Trials [11].

#### 2.1.2 *Eligibility criteria.*

Inclusion criteria:

(1)Patients with refractory epilepsy, including temporal lobe epilepsy, frontal lobe epilepsy, parietal lobe epilepsy, occipital lobe epilepsy, and insular gyrus epilepsy;(2)Patients with intracranial electrode implantation;(3)Patients with vascular anatomy that allows the EP-01 to be guided into the brain from the right and left jugular veins to vessels close to the presumed epileptic focus, such as the cavernous sinus, transverse sinus, superior sagittal sinus, and inferior petrosal sinus [the vessel into which the EP-01 will be placed will be determined by the physician, but the EP-01 must first be confirmed as able to be guided to a symmetrical position on both sides of the cerebral vein.]; and(4)Patient age 15–70 years (at the time of obtaining consent)

Exclusion criteria:

Potential enrollees who display any of the following criteria or enrollees who have provided consent and started participation but display any of the following criteria are to be excluded:

(1)Patients with epilepsy who have generalized seizures only;(2)Patients with obstruction or thrombus/thrombi in the internal jugular vein;(3)Patients with a predisposition to bleeding and coagulation abnormalities;(4)Patients with difficulty remaining still during procedures and/or measurements;(5)Patients with severe allergies to contrast media;(6)Patients with metal allergies;(7)Patients who are pregnant, become pregnant, or are of willful childbearing intent, including patients who fail to use the required birth control methods as outlined in the study protocol;(8)Patients participating in other clinical trials; or(9)Patients whom the investigator or sub-investigator determines at any time to be inappropriate to participate in this study

#### 2.1.3 *Planned intervention.*

The planned intervention is the insertion of the EP-01 endovascular EEG (EP-01 main unit and EP-01 accessories; Epsilon Medical Inc., Tokyo, Japan) and the use of devices to evaluate the efficacy and safety of the EP-01; namely, the EX-01 extension wire (Epsilon Medical Inc.) and EEG1200 series EEG (Neurofax/Nippon Kohden Corporation, Tokyo, Japan) that will be used to monitor data from the inserted EP-01.

The vessels for EP-01 placement would be determined by the principal investigator or sub-investigator depending on case circumstances from the following target areas: cavernous sinus, transverse sinus, superior sagittal sinus, and inferior petrosal sinus. In this protocol, placement of EP-01 in the cavernous sinus is considered particularly useful for determining lateralization in mesial temporal lobe epilepsy, as it is located immediately medial to the hippocampal head and amygdala [10]. In contrast, placement in the superior sagittal sinus (SSS), either in the anterior or posterior segments, is not primarily intended for determining lateralization. Instead, such placement is expected to be useful for comparison with other electrode sites and for evaluating the characteristics of epileptiform discharges. For these reasons, symmetrical anterior–posterior placement, as well as bilateral symmetry, is recommended.

The sheath to place the EP-01 will be implanted through the left and right jugular veins with the tip of the sheath pointing toward the cranial side. The microcatheters will then be inserted through the sheath to the target cerebral venous vessels. After verifying positioning (i.e., the exact vessel location), the EP-01 will be inserted into the microcatheter and delivered to the target site. After confirming successful delivery of the EP-01 to the target site, the microcatheter will be withdrawn, using an extension wire if necessary. After microcatheter removal, EEG data acquired at the electrode will be fed into the EEG measuring device via the lead wire. After confirming that the EEG is displayed on the measuring device, implantation of the EP-01 will be considered complete. After insertion is completed, a Tuohy Borst valve or silicone tubing will be used for proper fixation. After implanting a maximum of six wires, the wires protruding from the patient’s neck will be secured to complete the procedure.

To prevent thrombosis of the sheath during implantation of the EP-01 body, continuous perfusion of heparinized saline solution should be performed through the side port of the Tuohy Borst valve attached to the sheath as a rule. If the investigator determines that continuous irrigation with heparinized saline is difficult due to the condition of the subject, flush and lock will be performed at least once a day (heparinized saline is recommended for flushing and locking). During the period of EP-01 implantation, the position of the tip electrode should be confirmed by X-ray examination, and if the position of the tip electrode is found to be significantly misaligned, the safety of the subject will be given highest priority. In addition, the presence or absence of adverse events will be confirmed by CT. If adverse events are confirmed, appropriate treatments will be administered based on the judgment of the investigator.

Note that, because of the complex nature of the study, any therapy that, in the clinical judgment of the investigator or other associated care providers, is necessary for the benefit of the subject may be administered.

Prescribed drugs and therapies used from enrollment to the end of the post-observation period will be noted in the case report as concomitant medications and therapies. Concomitant medications and therapies used for intracranial electrode implantation (including additional implantation) and removal will not be recorded. If focal resection surgery is performed before the end of the post-observation period, concomitant medications and concomitant therapies used for these procedures are also excluded from recording. Antithrombotic therapy, however, will be documented in the case report as antithrombotic therapy from 30 days prior to obtaining consent until the end of the post-observation period.

The placement of intracranial electrodes (such as SDE or SEEG) will follow the insertion of EP-01s, but during the placement of intracranial electrodes, monopolar cautery is prohibited to minimize electrical interference, and head MRI is also not allowed after placement of EP-01s and intracranial electrodes.

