**Secondary endpoints.**

(1)Diagnostic performance of the EP-01 alone, without reliance on intracranial electrodes, for the diagnosis of lateralization of the epileptic focus. To be obtained by third-party evaluation via the Central Evaluation Committee.(2)If there is a period during which only EP-01 is placed, comparative evaluation will be conducted between the EEG measurement performance with EP-01 alone and with both EP-01 and intracranial electrodes in place, to ensure that there is no mutual interference.(3)To determine whether the waveforms detected by EP-01 are brain-generated EEG components, EEG changes with eyes open and closed will be observed. Evaluation will be conducted by a third party appointed by the Central Review Committee.(4)In the case of intracranial electrodes placed bilaterally, the percentage of agreement on lateralization of the epileptic focus between EP-01 EEG with noninvasive findings and findings from bilateral intracranial electrode EEG with noninvasive findings will be compared.(5)In the case of intracranial electrodes placed bilaterally, the percentage of agreement on lateralization of the epileptic focus between EP-01 EEG without noninvasive findings and findings from bilateral intracranial electrode EEG without noninvasive findings will be compared.(6)Diagnostic performance for the lateralization of the epileptic focus by EP-01 (percentage agreement with the results of diagnosis by intracranial electrodes with noninvasive findings) with noninvasive findings as evaluated by the primary investigators.(7)Epilepsy surgery outcome will be evaluated by the International League Against Epilepsy (ILAE) seizure outcome classification 1 year after focal resection.(8)Success rate of EP-01 implantation, calculated as the number of EP-01s implanted immediately after implantation/ number of microcatheters implanted x 100. In addition, whether the EP-01 has migrated from the target vessel will be evaluated immediately before removal.(9)Safety evaluations:aSeverity and temporal characteristics of adverse events (including medical procedures for implantation and removal of EP-01) and adverse events judged from imaging studies, etc., attributable to the study device (e.g., hemorrhage, midline shift, CSF leakage) (Each Primary Investigator evaluate whether the adverse events are attributable to EP-01 or invasive electrodes and ultimately compare which device is responsible for the adverse events)bIncidence and timing of adverse events (period of occurrence: from the start of use of the study device to the end of the post-observation period, including the start of use of the study device and the end of the post-observation period)cAssociations with all study devices (EP-01 body and EP-01 accessories), medical procedures for EP-01 implantation and removal, and other devices used in the study, judged by extent, severity, treatment, and outcome(10)Other evaluations:aFailure of EP-01 (EP-01 itself and EP-01 accessories)bOther failures of investigational devices (EX-01 extension wire/electroencephalograph)

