### 2.3 Monitoring

#### 2.3.1 *Data monitoring.*

The analysis of EEG data and device-related adverse events in this trial will be evaluated impartially by an independent review committee. The efficacy evaluation committee comprises four epilepsy specialists. Two will evaluate the EP-01 EEG, and two will assess intracranial EEG, ensuring the study remains blinded. The safety evaluation committee consists of three specialists: an epilepsy specialist, an endovascular neurosurgeon, and a radiation oncologist. Each will evaluate device-related adverse events from the perspective of their respective fields. None of the committee members have any conflicts of interest with the sponsor company.

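### The intracranial comparator is placed after EP-01 EEG can be seen, so EP-01 could influence its side or coverage, and blinded central reading does not protect against this

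*Protocol article*

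**What the plan says.** **Order.** Section 2.1.3 states: "The placement of intracranial electrodes (such as SDE or SEEG) will follow the insertion of EP-01s".

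**What the site can see.** Also in 2.1.3: "After confirming that the EEG is displayed on the measuring device, implantation of the EP-01 will be considered complete". Secondary endpoint (2) begins "If there is a period during which only EP-01 is placed", and the Fig 1 legend says of recording: "When only EP-01 or both EP-01 and intracranial electrodes are indwelled, EEG data from EP-01 and intracranial electrodes will be recorded under video surveillance". Secondary endpoint (6) is lateralization by EP-01 "with noninvasive findings as evaluated by the primary investigators", so site investigators are not blind to EP-01 throughout the trial.

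**The comparator.** Section 2.1.5 bases the intracranial determination on ictal intracranial EEG. Inclusion criterion (2) requires intracranial implantation without fixing side or extent. Secondary endpoints (4) and (5) treat bilateral placement as a subset, so the primary analysis also takes in one-sided arrays. Section 2.1.3 mentions further implantation in a sentence about medication records: "Concomitant medications and therapies used for intracranial electrode implantation (including additional implantation) and removal will not be recorded".

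**Blinding.** Section 2.3.1 says of the four efficacy readers: "Two will evaluate the EP-01 EEG, and two will assess intracranial EEG, ensuring the study remains blinded".

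**The concern.** The primary endpoint treats intracranial EEG as the standard against which EP-01 is judged, so the standard should be obtained independently of EP-01. The stated order puts EP-01 signal on a screen before the comparator exists, and in some patients may allow a longer EP-01-only recording first. If that signal moved, narrowed or extended the planned array towards the side EP-01 suggested, the intracranial record would be less able to contradict EP-01.

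Readers who see only one set of traces cannot correct this, because a one-sided array cannot show onset directly on the side it does not cover. Section 2.2.4 sets confounding aside because every participant receives both devices. That does not address one device influencing where the other is placed.

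The stake is the primary result: part of the observed agreement could be EP-01 agreeing with a comparator it helped to position.

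**Working it through.** **1. Reproduce the plan's figure.** Inputs from section 2.1.6: null agreement 0.80, expected agreement 0.97, one-sided exact binomial test at 0.025, power 90%, 34 evaluable, target 37.

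The pass mark is the smallest r with P(X ≥ r) ≤ 0.025 when X ~ Binomial(n, 0.80).

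| n | Pass mark | Discordances allowed | P(pass) at 0.80 | Power at 0.97 |
|---|---|---|---|---|
| 33 | 32 | 1 | 0.0059 | 0.740 |
| 34 | 32 | 2 | 0.0226 | 0.919 |
| 37 | 35 | 2 | 0.0135 | 0.901 |

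The stated 34 reproduces. No figure in the plan is wrong on this point. What matters here is that only two discordant patients are allowed at either size.

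**2. Does the stated text leave a route from EP-01 to the comparator?**
- EP-01 precedes the intracranial electrodes (2.1.3).
- Its EEG is on display before they go in (2.1.3), and EP-01-only recording is foreseen (Fig 1 legend; secondary endpoint 2).
- One-sided arrays count in the primary analysis (secondary endpoints 4 and 5 read against the primary endpoint).
- The only stated protection acts at central reading (2.3.1), after the electrodes have been sited.

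So the plan can be followed as written while EP-01 influences the comparator.

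**3. Illustrate the size.** The documents give no rate of influence. Assume m patients in whom agreement has become automatic, and agreement of 0.80 in the other n − m. The trial passes if at most two of those n − m patients are discordant:

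P(pass) = P(D ≤ 2), D ~ Binomial(n − m, 0.20).

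For n = 34, m = 5, n − m = 29 and the terms for 0, 1 and 2 discordances are 0.0016 + 0.0112 + 0.0393 = 0.052.

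| m (assumed) | n = 34 | n = 37 |
|---|---|---|
| 0 | 0.023 | 0.013 |
| 1 | 0.027 | 0.016 |
| 5 | 0.052 | 0.032 |
| 10 | 0.115 | 0.072 |

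**4. A second parameterisation.** Let s be the share of otherwise discordant patients turned concordant. Agreement becomes q = 0.80 + 0.20·s.

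| s (assumed) | q | P(pass), n = 34 | P(pass), n = 37 |
|---|---|---|---|
| 0 | 0.80 | 0.023 | 0.013 |
| 0.1 | 0.82 | 0.042 | 0.027 |
| 0.2 | 0.84 | 0.074 | 0.051 |
| 0.3 | 0.86 | 0.127 | 0.093 |

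Both models show that the error rate is sensitive to a few influenced patients. Neither says how many there will be.

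**The case against.** The strongest reply is that this is an argument from silence. The article condenses a full protocol that may fix the intracranial plan beforehand or keep EP-01 traces from those who choose it. That possibility stands. However, the order, the early display, the EP-01-only recording and the admission of one-sided arrays are all stated, and they create the dependence. The article also presents split reading as what keeps the study blinded.

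Several narrower replies hold and limit the point:

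- **Who implants.** A reader might infer that the same unblinded team places both devices. The article does not say who places the intracranial electrodes or what they have seen.
- **When EP-01 is alone.** Secondary endpoint (2) is conditional and gives no timing. Section 2.2.3 leaves removal of intracranial electrodes to clinical judgment, so an EP-01-only period could also come at the end. Similarly, display at insertion is a check that a signal exists rather than a lateralizing read, and endpoint (6) does not say when investigators make their reading.
- **Seizures before the comparator is in.** The first seizure is analysed (2.1.4), EP-01 stays in only until a seizure or the time limit (Fig 1 legend), and a patient with only one measurable device counts as discordant (2.2.4). A first seizure with EP-01 alone would therefore probably count against EP-01. What remains is mainly interictal signal.
- **Bilateral arrays.** A reader might infer that any array can be made to agree. Well-covered bilateral arrays are largely protected, and endpoints (4) and (5) already report agreement in bilaterally implanted patients, which is a partial check.
- **Prior hypothesis.** Eligibility rests on non-invasive findings and a presumed focus (2.1.2, 2.1.7), so a plan probably exists before EP-01. The article does not say that it is recorded.
- **Additional implantation.** The phrase comes from a sentence on medication records. It shows that arrays may be extended, but not when, where or why.

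**Conclusion.** The concern holds as a possible upward bias of unknown size. The stated sequence lets EP-01 signal reach the decision on the comparator's side or coverage, mainly through interictal discharges and mainly where arrays are one-sided or asymmetric. The blinding in 2.3.1 acts too late to prevent it.

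The article does not show that influence will occur, or that the comparator will be made to agree. The error rates calculated for influenced patients, including those for five automatic agreements, rest on assumed counts or shares, and automatic agreement is a worst case: a misplaced array may show no clear onset rather than a confirming one. They show only that a pass rule allowing two discordances has little room for such bias.

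The plan should be changed because the safeguard is cheap and the planned side cannot be reliably reconstructed afterwards. Confidence is medium, since the full protocol may already contain one.

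**What to change.** In section 2.1.3, add that the site records the planned side or sides, type and coverage of the intracranial electrodes, based on non-invasive findings and time-stamped before EP-01 insertion. Any later change or added electrode is recorded with its reason and whether EP-01 EEG had been viewed by then. This is a record only and does not restrict any clinical decision.

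In section 2.2.4, add a sensitivity analysis that repeats the primary agreement rate, with its Clopper–Pearson interval, without patients whose plan changed after EP-01 EEG was seen. Report it beside the bilateral-array results of secondary endpoints (4) and (5).

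The cost is one form page and a slightly smaller set in the sensitivity analysis. Sample size and the primary test stay as they are. If no plan changes, the record itself supports the comparator's independence. If the full protocol already requires this, one sentence in the article is enough.

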#### 2.1.4 Post-insertion examinations.

(1)EP-01 Placement Confirmation: The exact anatomical location (i.e., name of blood vessel) of the EP-01 tip electrode will be confirmed by X-ray examination (frontal and lateral) immediately after insertion, 1 day after insertion, 7 days after insertion, and immediately before removal. However, if the catheter is removed before 7 days, the observation timepoints after 7 days will be omitted(2)Adverse Event Check by CT: The presence or absence of adverse events from the EP-01 body insertion site will be confirmed by CT. Cone-beam CT (CBCT) is acceptable, as well as multislice CT, and three-dimensional (3D) data with slice thicknesses of 1 mm or less and 3–5 mm will be obtained(3)Electroencephalography: EEG data during eye opening and closing will be recorded. The timing of obtaining EEG data during open/closed eye movements will be at the discretion of the investigator. During a seizure that displays clinical symptoms, EP-01 EEG and intracranial electrode EEG will both be clearly recorded. The first seizure occurring after implantation will be analyzed. In this protocol, the use of an extracranial referential electrode at Fpz is recommended; however, each institution may determine the referential electrode to be used, provided that it allows for stable eEEG recording.

#### 2.1.5 Outcomes

***Primary endpoint.*** The primary endpoint is comparison of the lateralization diagnostic capability of EP-01 for epileptic foci with that of intracranial electrodes. Clinical findings, imaging findings obtained within one year prior to the date of consent (non-invasive findings), and EEG findings from scalp electrodes will be provided to a third party by the Central Review Committee. For intracranial electrodes, the determination of the epileptic foci will be based on ictal intracranial EEG findings. The lateralization diagnostic results of EP-01 for epileptic foci will then be compared with those obtained from intracranial electrodes, and the percentage agreement will be calculated.

**Secondary endpoints.**

(1)Diagnostic performance of the EP-01 alone, without reliance on intracranial electrodes, for the diagnosis of lateralization of the epileptic focus. To be obtained by third-party evaluation via the Central Evaluation Committee.(2)If there is a period during which only EP-01 is placed, comparative evaluation will be conducted between the EEG measurement performance with EP-01 alone and with both EP-01 and intracranial electrodes in place, to ensure that there is no mutual interference.(3)To determine whether the waveforms detected by EP-01 are brain-generated EEG components, EEG changes with eyes open and closed will be observed. Evaluation will be conducted by a third party appointed by the Central Review Committee.(4)In the case of intracranial electrodes placed bilaterally, the percentage of agreement on lateralization of the epileptic focus between EP-01 EEG with noninvasive findings and findings from bilateral intracranial electrode EEG with noninvasive findings will be compared.(5)In the case of intracranial electrodes placed bilaterally, the percentage of agreement on lateralization of the epileptic focus between EP-01 EEG without noninvasive findings and findings from bilateral intracranial electrode EEG without noninvasive findings will be compared.(6)Diagnostic performance for the lateralization of the epileptic focus by EP-01 (percentage agreement with the results of diagnosis by intracranial electrodes with noninvasive findings) with noninvasive findings as evaluated by the primary investigators.(7)Epilepsy surgery outcome will be evaluated by the International League Against Epilepsy (ILAE) seizure outcome classification 1 year after focal resection.(8)Success rate of EP-01 implantation, calculated as the number of EP-01s implanted immediately after implantation/ number of microcatheters implanted x 100. In addition, whether the EP-01 has migrated from the target vessel will be evaluated immediately before removal.(9)Safety evaluations:aSeverity and temporal characteristics of adverse events (including medical procedures for implantation and removal of EP-01) and adverse events judged from imaging studies, etc., attributable to the study device (e.g., hemorrhage, midline shift, CSF leakage) (Each Primary Investigator evaluate whether the adverse events are attributable to EP-01 or invasive electrodes and ultimately compare which device is responsible for the adverse events)bIncidence and timing of adverse events (period of occurrence: from the start of use of the study device to the end of the post-observation period, including the start of use of the study device and the end of the post-observation period)cAssociations with all study devices (EP-01 body and EP-01 accessories), medical procedures for EP-01 implantation and removal, and other devices used in the study, judged by extent, severity, treatment, and outcome(10)Other evaluations:aFailure of EP-01 (EP-01 itself and EP-01 accessories)bOther failures of investigational devices (EX-01 extension wire/electroencephalograph)

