
#### 2.1.6 *Sample size determination.*

The sample size is set at 37 using the following rationale: the null hypothesis is p = 0.8 and the alternative hypothesis is p > 0.8 for the statistical analysis of the lateralization diagnosis of EP-01 to intracranial electrode insertion concordance ratio. The hypothesis will be tested using an exact one-tailed test of binomial proportions. Assuming an expected percentage agreement of 0.97, a significance level of 0.025, and a power of 90%, the required number of cases is 34. Considering a 10% dropout rate, the target number of cases will be increased to 37.

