#### 2.2.3 *Follow-up.*

The EP-01 main unit is to stay implanted for up to 2 weeks (plus up to 3 days allowance) and then be removed. Intracranial electrodes will be removed according to clinical judgment and may be removed at the same time as the EP-01 unit. A follow-up period of 1 year will be conducted to evaluate the seizure-free rate after focal resection using data obtained from the EP-01 unit.

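### Secondary endpoint 2 is meant to exclude interference in both directions, but its comparison can inform only the effect of the intracranial electrodes on EP-01

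*Protocol article*

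**What the plan says.** Section 2.1.5, secondary endpoint 2, is conditional: "If there is a period during which only EP-01 is placed". In that case "comparative evaluation will be conducted between the EEG measurement performance with EP-01 alone and with both EP-01 and intracranial electrodes in place". The stated purpose is "to ensure that there is no mutual interference".

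Four other places bear on it:

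- **Order of insertion (2.1.3):** "The placement of intracranial electrodes (such as SDE or SEEG) will follow the insertion of EP-01s".
- **Recording (Fig 1 legend):** "When only EP-01 or both EP-01 and intracranial electrodes are indwelled, EEG data from EP-01 and intracranial electrodes will be recorded under video surveillance".
- **Removal (2.2.3):** "Intracranial electrodes will be removed according to clinical judgment and may be removed at the same time as the EP-01 unit".
- **Role of the intracranial recording (2.1.5, primary endpoint):** "The lateralization diagnostic results of EP-01 for epileptic foci will then be compared with those obtained from intracranial electrodes".

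**The concern.** The purpose and the comparison of endpoint 2 do not match. The purpose covers two effects: intracranial electrodes acting on the EP-01 signal, and EP-01 acting on the intracranial signal. The comparison has a with-and-without contrast for the first effect only.

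The missing direction is not a side issue, because it concerns the reference. Section 2.1.4 requires both signals to be recorded during the analysed seizure, so the intracranial reading behind the primary endpoint is made with EP-01 in place. Endpoint 2 is the only stated check on whether the two devices disturb each other. If the trial reported from it that there was no mutual interference, readers would take the reference as having been checked, and it would not have been.

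No choice of metric in an analysis plan can repair this. However measurement performance is defined, a state without intracranial electrodes yields no value for the intracranial signal.

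**Working it through.** Endpoint 2 carries no figure, hypothesis or success criterion, so there is nothing to recompute. The check is to list the device states and ask which signal is available in each.

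| Device state | EP-01 signal | Intracranial signal | Used in endpoint 2? |
|---|---|---|---|
| EP-01 only | yes | none | yes, if the period exists |
| Both in place | yes | yes | yes |
| Intracranial only, before EP-01 | none | none: intracranial placement follows EP-01 (2.1.3) | no |
| Intracranial only, after EP-01 removal | none | possible, not required (2.2.3) | no |

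The two effects, in terms of any chosen measure of recording quality, are:

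- **Intracranial electrodes on EP-01** = EP-01 signal (both in place) minus EP-01 signal (EP-01 only). Both terms are in the plan, so the contrast can be formed.
- **EP-01 on intracranial electrodes** = intracranial signal (both in place) minus intracranial signal (intracranial only). The second term is in no endpoint, and the Fig 1 legend does not list that state among those recorded for the trial.

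The EP-01 signal is thus seen in two states and the intracranial signal in one. The second effect cannot be estimated from the data that the article describes.

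I then looked for another source of the missing term. The insertion order rules out an intracranial-only baseline before EP-01. Section 2.2.3 leaves intracranial removal to clinical judgment, so a later intracranial-only period may arise, but no endpoint uses it. The remaining secondary endpoints address lateralization, eye opening and closing on the EP-01 recording, surgical outcome, implantation success, safety and device failure. None compares intracranial EEG with and without EP-01.

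The first effect is also limited by the condition in endpoint 2: a patient with no EP-01-only period contributes to neither direction. The article does not say how many patients will have such a period, or how many will have an intracranial-only period.

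**The case against.** The strongest case on the other side has four parts.

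**It is a conditional secondary check.** The only confirmatory test is on agreement, where "the null hypothesis is p = 0.8 and the alternative hypothesis is p > 0.8", and it does not use endpoint 2. This is correct. The point does not touch the type I error, the power or the target of 37 patients.

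**Primary agreement need not be affected.** A reader might infer that the agreement percentage is distorted. The document does not support that. The intracranial determination rests on ictal findings (2.1.5) in a seizure with clinical symptoms (2.1.4). Separate pairs of specialists read the two recordings blinded (2.3.1). Bilaterally symmetrical placement is recommended (2.1.3). To inflate agreement, artefact would have to resemble a lateralised ictal onset on the same side in both recordings. Artefact that made only the intracranial recording unmeasurable would count as discordant (2.2.4), which works against the device. These features make a false agreement less likely; they do not show that EP-01 leaves the intracranial signal unchanged.

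**The order of periods is not fixed.** A reader might also infer that the EP-01-only period must come first. Section 2.1.3 fixes only the order of insertion, and section 2.2.3 does not exclude intracranial removal before EP-01, which would give a later EP-01-only period. What stands is weaker: an EP-01-only period that arises from the insertion sequence comes before the intracranial operation, so that contrast will usually be mixed with surgery and elapsed time.

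**The article condenses a fuller protocol.** The Fig 1 legend does not say that intracranial recording stops when EP-01 is removed, and detailed recording rules may be elsewhere. That is fair. But the article states both the purpose and the comparison of endpoint 2, and these two do not match. The point rests on that mismatch and not on missing detail.

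**Conclusion.** The point holds in a limited form. As written, endpoint 2 can support a statement about the effect of intracranial electrodes on EP-01. It cannot support a statement about the effect of EP-01 on the intracranial recording, so a conclusion of no mutual interference would be unsupported in that direction.

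Its size is one of two claimed directions left without a comparator. The untested one concerns the recording that serves as reference for the primary endpoint. No numerical effect on the agreement estimate follows from the document, and there is no evidence in it that interference occurs.

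The conclusion assumes that mutual is meant in its ordinary two-way sense, and that the full protocol contains no with-and-without comparison of intracranial EEG that the article left out. It is worth correcting before results are reported, but it does not threaten the confirmatory analysis.

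**What to change.** 1. **Narrow the aim (always possible).** Reword the purpose and the permitted conclusion of endpoint 2 to the effect of intracranial electrodes on the EP-01 recording.
2. **Add the other direction where the data arise anyway.** In patients whose intracranial electrodes stay in after EP-01 removal for clinical reasons, retain short resting and eyes-open/eyes-closed intracranial segments. Compare them descriptively with matching segments from the period with both devices in place. Add this state to the recording rule in the Fig 1 legend.
3. **Tie the claim to the data.** State absence of mutual interference only from patients who have both comparisons, and report how many there are.
4. **State the limitation.** Both contrasts are before-and-after comparisons and are confounded with elapsed time. The EP-01 contrast is usually also confounded with the intracranial operation. The intracranial contrast may often follow a seizure, because EP-01 may stay in until one occurs (Fig 1 legend). The added intracranial contrast concerns a different signal and a different device change, so it is no check on order effects in the EP-01 contrast.

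The cost is a small amount of data handling and one more descriptive comparison, with no added procedure, no longer implantation and no change to clinical decisions. The number of eligible patients is unknown and may be small; if there are none, step 1 alone applies.
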